### Phase 4: Follow-up mailed survey at 18 months (Phase 2 respondents only)

Follow-up surveys will be mailed to all Phase 2 participants 18 months after their baseline clinical assessment. The focus of follow-up will be clinical (severity of pain and functional limitation) change and possible determinants of this. The content of this survey is provided in Table 3. Non-responders to the questionnaire will be sent a reminder postcard after two weeks. Those who do not respond to the reminder postcard will be sent a repeat questionnaire and Participant Information Sheet with a further covering letter four weeks after the initial mailing. Primary outcome data will be sought from non-respondents by telephone interview or shortened postal questionnaire. We plan to trace participants who have moved practice during the follow-up period using the NHS tracing service.

**Table 3 T3:** Content of 18-month postal follow-up Health Survey questionnaire (Phase 2 participants only)

Concept	Measurement method	Detail
Foot pain characteristics	Change in foot pain over past 18 months	Completely recovered, much better, better, no change, worse, much worse
	Since your assessment 18 months ago, have you ever injured your foot badly enough to see a doctor about it?	No/right only/left only/both
	Foot pain, aching, stiffness in last month [39]	No days, few days, some days, most days, all days
	Foot pain intensity in past month [40]	0-10 NRS with verbal anchors (no pain, pain as bad as could be)
Foot pain chronicity	Chronic Pain Grade [59]	6 questions (0-10 NRS) and 1 question (4 response options) giving grade I-IV
Complaint-specific functioning	Manchester Foot Pain and Disability Index [41]	19-items across four constructs: pain, function, appearance, work/leisure
	Symptom satisfaction [64]	5-point Likert scale (Very dissatisfied to Very satisfied)
Healthcare use	Use of services/treatments for foot pain in past 18 months	GP, physiotherapist, hospital specialist, acupuncture, podiatrist, chiropodist, drugs on prescription, foot injection, foot surgery, osteopath/chiropractor, other (specify)
	Medication use in last month	For foot pain, for other pain
Coping strategies for foot pain	Single-item coping strategies questionnaire [42]	0-6 NRS with verbal anchors (never do that, always do that)
Perceived general health	MOS SF 12 [33]	Physical and mental component summary scores
Physical function	MOS SF 36 [32]	Physical functioning sub-scale
Anxiety and depression	Hospital anxiety and depression scale [34]	Anxiety and depression sub-scales
Hallux valgus	Self-completed line drawings [37]	5 line-drawings for each foot depicting increasing severity of hallux valgus
Bodily pain	Self-completed body manikin	In the past 4 weeks, have you had pain that has lasted for one day or longer in any part of your body? If yes, shade location of pain on manikin
Regional pain	Site-specific questions	Have you had any problems with your hands or pain in your hands/hips/knees in the last year?
Demographic characteristics	Date of birth Gender	
Socioeconomic characteristics	Current employment status	Employed, not working due to ill-health, retired, unemployed/seeking work, housewife, other

MOS SF 12 = Medical Outcomes Study Short Form 12; MOS SF 36 = Medical Outcomes Study Short Form 36; NRS = numerical rating scale

### Phase 5: Follow-up mailed survey at 3 years (Phase 1 and Phase 2 respondents)

Follow-up surveys will be mailed to all Phase 1 and 2 participants 3 years after their baseline Health Survey questionnaire. In addition to information about clinical change in Phase 2 participants, the survey will also include repeat measures of lifestyle [36,73], general health (including generic measures of physical function [32,33]), psychosocial factors [34], co-morbidity [37,38] and basic screening questions concerning the presence [39], duration, location [14], severity [40], and impact of foot pain [41,42] (Table 4). Non-responders to the questionnaire will be sent a reminder postcard after two weeks. Those who do not respond to the reminder postcard will be sent a repeat questionnaire and Participant Information Sheet with a further covering letter four weeks after the initial mailing. Primary outcome data will be sought from non-respondents by telephone interview (Phase 2 participants only) or shortened postal questionnaire. We plan to trace participants who have moved practice during the follow-up period using the NHS tracing service.

**Table 4 T4:** Content of 3-year postal follow-up Health Survey questionnaire (Phase 1 and Phase 2 participants)

Concept	Measurement method	Detail
**Section A: General health**		
Perceived general health	MOS SF 12 [33]	Physical and mental component summary scores
Physical function	MOS SF 36 [32]	Physical functioning sub-scale
Anxiety and depression	Hospital anxiety and depression scale [34]	Anxiety and depression sub-scales
Participation	Keele Assessment of Participation (KAP) [35,73]	5-items assessing person-perceived, performance-based participation
Physical activity	Short-Form International Physical Activity Questionnaire (IPAQ) [36]	Frequency and duration of 4 activities performed during previous 7 days
		
**Section B: Specific health problems**		
Hallux valgus	Self-completed line drawings [37]	5 line-drawings for each foot depicting increasing severity of hallux valgus
Co-morbidities	Falls, fractures, chest problems, heart problems, deafness, problems with eyesight, raised blood pressure, diabetes, stroke, cancer, liver disease, kidney disease, poor circulation, rheumatoid arthritis	Yes for any that apply
Intermittent claudication	Edinburgh Claudication Questionnaire [38]	Pain or discomfort in legs when walking, pain characteristics, pain location (leg manikin)
Bodily pain	Self-completed body manikin	In the past 4 weeks, have you had pain that has lasted for one day or longer in any part of your body? If yes, shade location of pain on manikin
	Site-specific questions	Have you had any problems with your hands or pain in your hands/hips/knees/feet in the last year?
		
**Section C: Foot pain**		
Foot pain characteristics	Side of pain	Both, right, left
	Duration in past 12 months	< 7 days, 1-4 weeks, 1-3 months, 3+ months
	Have you ever injured your foot badly enough to see a doctor about it?	No/right foot only/left foot only/both feet
	Location: self-completed foot manikin [14]	In the past month, have you had any ache or pain that has lasted for one day or longer in your feet? If yes, shade location of pain on foot manikin
	Foot pain, aching, stiffness in last month [39]	No days, few days, some days, most days, all days
	Foot pain intensity in last month [40]	0-10 NRS with verbal anchors (no pain, pain as bad as could be)
Complaint-specific functioning	Manchester Foot Pain and Disability Index [41]	19-items across four constructs: pain, function, appearance, work/leisure
Coping strategies for foot pain	Single-item coping strategies questionnaire [42]	0-6 NRS with verbal anchors (never do that, always do that)
Healthcare use	Medication use in last month	For foot pain, for other pain
	Consultation with general practitioner in last 12 months for foot pain	
		
**Section D: Demographic/socioeconomic characteristics**		
Demographic characteristics	Date of birth Gender	
	Marital status	Married, separated, divorced, widowed, cohabiting, single
	Living arrangements	Alone, not alone
Anthropometric characteristics	Self-reported height	
	Self-reported weight	
Socioeconomic characteristics	Current employment status	Employed, not working due to ill-health, retired, unemployed/seeking work, housewife, other
	Current/recent job title	Free text
	Current/recent job title of spouse	Free text
	Adequacy of income [43]	Find it a strain to get by from week to week, have to be careful with money, able to manage without much difficulty, quite comfortably off
**Additional questions for phase 2 participants only**		
Foot pain characteristics	Change in foot pain over past 3 years	Completely recovered, much better, better, no change, worse, much worse
	Since your assessment 3 years ago, have you injured your foot badly enough to see a doctor about it?	No/right foot only/left foot only/both feet
Foot pain severity	Chronic Pain Grade [59]	6 questions (0-10 NRS) and 1 question (4 response options) giving grade I-IV
	Symptom satisfaction [64]	5-point Likert scale (Very dissatisfied to Very satisfied)
Healthcare use	Use of services/treatments for foot pain in past 3 years	GP, physiotherapist, hospital specialist, acupuncture, podiatrist, chiropodist, drugs on prescription, foot injection, foot surgery, osteopath/chiropractor, other (specify)

MOS SF 12 = Medical Outcomes Study Short Form 12; MOS SF 36 = Medical Outcomes Study Short Form 36; NRS = numerical rating scale

### Sample size

The sample size for this study was determined by the estimated numbers of participants needed in Phase 2 in order to ensure sufficient power for both cross-sectional and longitudinal analyses. The primary aim is to compare the proportion of participants with poor functional outcome across the radiographic (p_2_) and no radiographic OA groups (p_1_) at 3 years. Assuming p_1 _= 20% in the unexposed group, a sample size of 426 will have 80% power to detect a relative risk (p_2_/p_1_) of 1.62 using a 5% significance level. Allowing for a drop-out figure of 80 from baseline to three years will require an initial recruitment of 506 participants to Phase 2.

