In addition to the questions of what phenotypes present to primary care and how they are managed, a crucially important issue is what effect primary care management has on outcome. Non-consultation for peripheral joint problems is common. Approximately 80% of those with musculoskeletal foot problems do not appear to consult their GP over prolonged periods of time (three years) [28]. Part of this is likely be related to the belief, pervasive among both the public and practitioners, that "nothing can be done". Furthermore, despite randomised controlled trial evidence about the short-term efficacy of primary care treatment for some peripheral joint problems [29], there are few investigations of the long-term effect of primary care consultation or OA management on impairment, activities or participation.

In summary, there is a paucity of research evidence concerning the radiographic phenotypes of foot OA and their impact on symptoms, clinical features, activity limitation and participation restriction. Important questions concerning how clinical phenotypes relate to the diagnosis of OA in primary care, and how the outcome from foot pain and OA is influenced by primary care consultation have been under-researched in relation to the foot but also at other joint sites. This prospective, observational, cohort study will combine unselected population sampling of older adults, self-reported survey data, comprehensive clinical and radiographic assessment, and linkage to computerised primary care records, to address these issues over a three-year period. It is designed to complement earlier studies of knee pain and OA [30] and hand pain, problems and OA [31] and permit combining of data across all three cohorts as well as direct comparison between them.

The aims of the study are to:

(i) Describe the frequency and pattern of co-occurrence of radiographic features of symptomatic OA in the following foot joints: the 1^st ^MTPJ, the 1^st ^and 2^nd ^CMJs, the NCJ and the TNJ.

(ii) Relate the occurrence of radiographic OA, described above, cross-sectionally to foot pain and disability, foot deformities, and soft tissue problems on physical examination. The associations between foot OA, foot pain, disability and footwear will also be examined.

(iii) Determine prospectively the factors that predict clinical deterioration, for example, radiographic OA, footwear characteristics, pain/OA at other sites, and psychosocial factors.

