#### Outcome of foot OA at 3 years

Linking baseline date to 18-month and three-year follow-up questionnaires, we will then be able to determine prospectively the factors that are related to clinical deterioration using risk ratios and associated 95% confidence intervals, for example, radiographic OA, footwear characteristics, pain/OA at other sites, psychosocial factors.

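### The study is sized on a 3-year proportion with poor functional outcome, while the aims list and the 3-year analysis name clinical deterioration, so 426 is not shown to give 80% power for the outcome analysed

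*Protocol article*

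**What the plan says.** Sample size in the protocol article names one primary comparison: "The primary aim is to compare the proportion of participants with poor functional outcome across the radiographic". The comparator is the group without radiographic OA, and the time point is three years. The planning values begin with "Assuming p_1 _= 20% in the unexposed group". On that basis the article concludes that "a sample size of 426 will have 80% power to detect a relative risk (p_2_/p_1_) of 1.62", taking the significance level as 5%. Adding 80 drop-outs gives 506. The same section says the Phase 2 numbers are meant to give enough power for both the cross-sectional and the longitudinal analyses.

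The six aims at the end of Background contain no such comparison. The longitudinal aim that involves radiographic OA is (iii): "Determine prospectively the factors that predict clinical deterioration", with radiographic OA as one example among several factors. The analysis section Outcome of foot OA at 3 years follows aim (iii): it will "determine prospectively the factors that are related to clinical deterioration using risk ratios". The Phase 4 section says of the follow-up: "The focus of follow-up will be clinical (severity of pain and functional limitation) change and possible determinants of this".

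Phase 2 is open only to survey responders who report foot pain in the previous twelve months. Covariates (age, gender, BMI) are named for the cross-sectional odds ratios. The 3-year risk ratios carry no statement on baseline function.

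**The concern.** The outcome that set the sample size and the outcome analysed at 3 years have different names and, on their natural reading, are different quantities. A proportion with poor function at 3 years is a state. Deterioration is a change from the participant's own starting point. Someone with poor function at entry who stays the same counts as an event on the first reading but would not normally count on the second.

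Two things are at stake. First, the 20%, the 1.62 and the 426 belong to the first quantity and do not automatically carry over to the second. Second, the cohort is symptomatic at entry, and aim (ii) asks whether radiographic OA goes with disability at baseline. An imbalance in baseline function between the OA groups is therefore plausible, and an unconditioned 3-year contrast would pass part of it on.

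There is also a practical consequence. The follow-up sections plan to chase primary outcome data from non-respondents, and two analysis sections plan to impute missing primary outcome data. Both need a single identified primary outcome.

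**Working it through.** **1. Reproducing the 426.** Inputs from Sample size: p1 = 0.20, relative risk 1.62, so p2 = 0.324, difference d = 0.124, mean 0.262; 5% level, 80% power. Assumed because they reproduce the figure: two-sided test, equal groups.

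n = [1.96 × √(2 × 0.262 × 0.738) + 0.842 × √(0.20 × 0.80 + 0.324 × 0.676)]² / 0.124² = (1.2188 + 0.5181)² / 0.015376 = 196.2 per group, i.e. 197, or 394 in total.

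With continuity correction: (n/4) × [1 + √(1 + 4/(n × d))]² = 49.05 × (1 + √1.1644)² = 212.04, i.e. 213 per group, or 426 in total. Then 426 + 80 = 506. The arithmetic is sound for a 20% unexposed risk.

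**2. Tracing the outcome through the article.**

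| Place | 3-year quantity |
|---|---|
| Aims (i) to (vi) | deterioration (aim iii); no poor-function comparison |
| Sample size | proportion with poor functional outcome, by radiographic OA |
| Phase 4 | change in pain severity and functional limitation |
| Outcome of foot OA at 3 years | deterioration, by risk ratio |
| Modelling the outcomes of care | effects of care, not of radiographic OA |

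The comparison called primary appears only in Sample size.

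**3. How much a baseline difference can pass through.** The documents give no baseline prevalence of poor function, no persistence and no incidence, so these are assumptions. Let b be baseline prevalence, s the proportion of those who stay poor, and i the proportion of the rest who become poor, with s and i equal in both OA groups (no effect on deterioration). Then p(3 years) = i(1 − b) + s × b. Fixing the unexposed group at 20% gives i = (0.20 − s × b0)/(1 − b0). For a baseline ratio r, the 3-year ratio is 1 + (s − i) × b0 × (r − 1)/0.20.

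- b0 = 15%, s = 60%: i = 0.11/0.85 = 0.129. With r = 1.62 the 3-year ratio is 1 + 0.471 × 0.15 × 0.62/0.20 = 1.22.
- b0 = 18%, s = 80%: i = 0.056/0.82 = 0.068. With r = 1.62 the 3-year ratio is 1 + 0.732 × 0.18 × 0.62/0.20 = 1.41.

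For b0 of 15–18% and s of 60–80%, a baseline ratio of 1.62 therefore gives 1.22 to 1.41. That is 4.4 to 8.2 of the planned 12.4 percentage points (about 35% to 66%), with a 19% to 50% chance of a significant result at 213 per group. A baseline ratio of 2.0 gives 1.35 to 1.66 and a 40% to 87% chance.

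Reproducing the full 1.62 with no effect on deterioration needs r = 1 + 0.124/[(s − i) × b0]. With i = 10%, s = 70%, b0 = 16.7% this is 2.24. With i = 5%, s = 80%, b0 = 20% it is 1.83.

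**4. What 426 gives for deterioration.** The deterioration risk is not stated, so a range is shown (relative risk 1.62, two-sided 5%, 80% power, 1:1). The last column takes deterioration to mean new poor function among those without it at baseline, with baseline prevalence 10–20% in the unexposed and 1.62 times that in the OA group. Of 426 followed, 213 × 0.90 + 213 × 0.838 = 370 down to 213 × 0.80 + 213 × 0.676 = 314 are then at risk.

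| Unexposed risk | Total N needed, uncorrected | Power with 314–370 at risk, uncorrected |
|---|---|---|
| 20% | 394 | 71–78% |
| 15% | 572 | 55–62% |
| 10% | 928 | 38–43% |
| 5% | 1,998 | 20–23% |

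On the same uncorrected basis, 213 per group gives 83% power for the planned 20% versus 32.4%.

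**The case against.** The strongest reply is that poor functional outcome is not defined in the article. It stands beside the words relative risk and unexposed group, and the full protocol or analysis plan may define it by change or condition it on baseline function. An article often leaves operational definitions and covariates to those documents. This stands as far as it goes: the missing definition and the missing adjustment set are not faults in themselves. It does not remove the mismatch. If change was meant, Sample size uses a different term from the aims and from the 3-year analysis, and a proportion at 3 years reads as a state.

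A reader might infer that the primary contrast largely carries forward baseline differences. The documents do not support that. Every rate in step 3 is assumed, and reproducing the whole 1.62 takes baseline ratios of about 1.8 to 2.2, larger than the target effect itself. What the check supports is that part of the contrast can come from baseline.

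A reader might also infer that aim (iii) goes unanswered. It does not: Outcome of foot OA at 3 years analyses deterioration directly. The gap lies in the sizing and in the primary label. Nor is the calculation wrong, since 426 reproduces exactly.

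Finally, it is tempting to insist on analysing only participants without poor function at baseline. That is one option, but it drops any worsening among those already poor and loses power, so it should not be prescribed.

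**Conclusion.** The point holds as an internal inconsistency with a real consequence for interpretation. The comparison that sizes the study and is called primary is neither among the aims nor analysed under that name, and the 3-year analysis addresses deterioration.

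How far baseline differences would enter an unconditioned 3-year contrast depends on figures the documents do not give. A 3-year ratio of about 1.2 to 1.4 from a baseline ratio of 1.62 illustrates the scale and is not an estimate for this cohort. In the same way, 80% power is shown for a 20% unexposed risk only. Whether it holds for deterioration depends on a rate not stated, and on the incident-only reading it falls short at every risk tabulated. The matter should be settled before the 3-year result is read as prognosis.

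**What to change.** - Name one primary 3-year outcome and use the same term in the aims, in Sample size and in Outcome of foot OA at 3 years.
- State whether the 20% is the proportion with poor function at 3 years or the risk of deterioration.
- Estimate the 3-year risk ratio conditional on baseline function on the same instrument, either the Manchester Foot Pain and Disability Index or SF-36 physical functioning. Do this by adjustment or by stratifying on poor function at baseline.
- If the outcome is deterioration, restate the relative risk that 426 can detect at the assumed deterioration rate. If the 3-year state is kept, describe it as the burden of poor function at 3 years rather than as evidence on deterioration.

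Cost: wording in three places and a short recalculation. Both instruments are already collected at baseline, 18 months and 3 years (Tables 1, 3 and 4), so no new data are needed. The stated detectable relative risk may become less favourable, and more so if the deterioration rate is well below 20%.

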### Statistical analysis

#### Patterns of symptomatic radiographic foot OA

The frequency and co-occurrence of radiographic features of symptomatic OA at the 1^st ^MTPJ, the 1^st ^and 2^nd ^CMJs, the NCJ and the TNJ will be described using simple descriptive statistics.

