## Abstract

**Background:**

Symptomatic osteoarthritis (OA) affects approximately 10% of adults aged over 60 years. The foot joint complex is commonly affected by OA, yet there is relatively little research into OA of the foot, compared with other frequently affected sites such as the knee and hand. Existing epidemiological studies of foot OA have focussed predominantly on the first metatarsophalangeal joint at the expense of other joints. This three-year prospective population-based observational cohort study will describe the prevalence of symptomatic radiographic foot OA, relate its occurrence to symptoms, examination findings and life-style-factors, describe the natural history of foot OA, and examine how it presents to, and is diagnosed and managed in primary care.

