### Phase 1: Baseline postal Health Survey questionnaire

All adults aged 50 years and over registered with four local general practices (mailed population approximately 9000 adults) will be mailed a letter of invitation from their general practitioner, a Participant Information Sheet, a Health Survey questionnaire, and a pre-paid return envelope. The lead general practitioner (GP) at each practice will be invited to identify potentially vulnerable patients (e.g. dementia, severe or terminal illnesses) they feel should be excluded from the study. Practice lists will be screened prior to mailing to ensure that addresses are up to date and exclude any recent deaths or departures from the practice list. Health Survey questionnaires will be mailed in batches (n = 500) to ensure regular recruitment to research clinics (Phase 2) and to limit the interval between questionnaire completion and clinic attendance. Pilot cognitive interviews have been undertaken with members of the Research Centre's Research User Group to test the Health Survey questionnaire's layout, readability, content, language and length. The questionnaire will be divided into five main sections: (i) general health (including generic measures of physical function, psychosocial factors and lifestyle [32-36] (Additional File 1: Appendix 1)); (ii) specific health problems including musculoskeletal co-morbidity and pain [37,38]; (iii) questions concerning the presence [39], duration, location [14], severity [40], and impact [41,42] of foot pain; (iv) demographic and socioeconomic characteristics [43,44]; and (v) employment (Table 1). Non-responders to the questionnaire will be sent a reminder postcard after two weeks. Those who do not respond to the reminder postcard will be sent a repeat questionnaire and Participant Information Sheet with a further covering letter four weeks after the initial mailing. Questionnaires will ask for consent (i) to contact participants again by post and/or (ii) to review medical records. Responders will be given the option of providing their telephone number for further contact.

**Table 1 T1:** Content of baseline postal Health Survey questionnaire

Concept	Measurement method	Detail

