### Phase 2: Baseline Clinical Assessment Study of the Foot (CASF)

Responders to the Health Survey questionnaire who report experiencing pain in or around the foot within the last twelve months and who provide written consent to further contact will be sent a letter of invitation to attend a research clinic. The letter of invitation will be accompanied by a Participant Information Sheet providing details of the study. Participants will be asked to telephone the Research Centre if they are interested in taking part in order to book an appointment. Non-responders to this initial invitation letter will be sent a reminder invitation approximately two weeks later.

Those willing to take part in the study will be booked into the next convenient appointment and, if necessary, travel arrangements (taxi) made. Postal confirmation of the appointment will be made by letter and then by a reminder postcard shortly prior to the appointment. The postcard will be mailed in an envelope to maintain confidentiality about the nature of the appointment. Participants who do not attend the clinic for their specified appointment will be sent another letter asking them to re-contact the Research Centre and book another appointment if they still wish to participate.

Assessment clinics for the study will be conducted twice-weekly in a local NHS Trust community rheumatology hospital. A maximum of 12 appointments per week are scheduled. Each clinic is to be staffed by a Clinic Co-ordinator, a Clinic Support Worker, two trained Health Professionals (podiatrist or physiotherapist) acting as Research Assessors, one trained Research Assessor (physiotherapist, radiographer or nurse) acting as an Ultrasonographer, and two Radiographers.

On arriving at clinic, participants will be issued with a file containing all assessment documentation marked with their unique study number. Prior to commencing the assessment, the procedures outlined in the Participant Information Sheet will be discussed with each participant. Participants will be given the opportunity to ask questions. Written informed consent to take part in the study will be obtained from all participants. Appropriate clothing (shorts) for the assessment will be provided.

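### The abstract promises prevalence of symptomatic radiographic foot OA, but the planned analysis gives only a frequency among symptomatic clinic attenders

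*Protocol article*

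**What the plan says.** The abstract of the protocol article states: "This three-year prospective population-based observational cohort study will describe the prevalence of symptomatic radiographic foot OA". Aim (i), in the Background, is worded differently: "Describe the frequency and pattern of co-occurrence of radiographic features of symptomatic OA in the following foot joints". The analysis section headed Patterns of symptomatic radiographic foot OA follows the aim. It says that frequency and co-occurrence at the listed joints, ending with "the NCJ and the TNJ will be described using simple descriptive statistics". It names no target population, denominator, weighting or interval.

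The route to an x-ray is set out under Phases 1 and 2. The frame is the list of four practices ("mailed population approximately 9000 adults"), less those removed after the lead GP is "invited to identify potentially vulnerable patients". A person must then return the survey, report foot pain in the past year, agree to further contact, and opt in: "Participants will be asked to telephone the Research Centre if they are interested in taking part in order to book an appointment". Finally the person must attend. Radiographs are planned only for those attending the Phase 2 clinic.

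**The concern.** The abstract and the analysis section describe different quantities. A simple frequency among people x-rayed is conditional on having foot pain and on attending. Prevalence in the registered population is not conditional on either.

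Two separate issues arise. The first is the denominator: the clinic proportion has to be multiplied by the prevalence of foot pain before it refers to the population. The second is selection among people who do have foot pain, through survey non-response, refusal of further contact, and failure to telephone or attend. Absence of foot pain belongs to the case definition and is not selection bias.

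At stake is the study's first descriptive result. Read alongside the abstract, a clinic frequency could be taken for a population prevalence that the planned analysis does not estimate.

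**Working it through.** **1. The plan's own figure.** Sample size section: p1 = 0.20, relative risk 1.62, so p2 = 0.324; 80% power; 5% significance level. The section does not state sidedness, allocation or continuity correction. With a two-sided test, equal groups and a continuity correction, the standard two-proportion formula gives 213 per group, or 426 in total, which matches. Without the correction it gives 394. Adding 80 for drop-out, 426 + 80 = 506. This number serves the 3-year comparison and was not chosen for estimating prevalence.

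**2. What 506 of 9000 means.** 506/9000 = 5.6%. Most of the people outside the clinic may have no foot pain, so this is not a participation rate. The documents give no response rate, foot-pain prevalence, clinic uptake or OA proportion; the values below are assumptions. With survey response of 50% to 70% and foot pain in 20% to 40% of responders:
- fewest with foot pain: 9000 × 0.5 × 0.2 = 900, and 506/900 = 56%
- most with foot pain: 9000 × 0.7 × 0.4 = 2520, and 506/2520 = 20%

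So 506 attenders would be roughly 20% to 56% of the responders with foot pain.

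**3. The denominator alone.** Prevalence among responders = P(foot pain) × P(OA given foot pain). Assume 50% OA among attenders and no selection bias:
- foot pain 20%: 0.20 × 0.50 = 10%
- foot pain 40%: 0.40 × 0.50 = 20%

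The clinic frequency would read 50%. Dividing cases by everyone mailed fails the other way: 0.50 × 506 = 253, and 253/9000 = 2.8%, which counts every unexamined person as free of OA.

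**4. Adding selection among people with foot pain.** Let a be the attending fraction, q the OA proportion in attenders and q′ that in eligible non-attenders. Prevalence among responders = P(foot pain) × [a·q + (1 − a)·q′]. Assume response 60%, foot pain 30%, q = 0.50. Then 9000 × 0.6 × 0.3 = 1620 and a = 506/1620 = 0.312.
- q′ = 0.25: 0.30 × (0.156 + 0.172) = 9.8%
- q′ = 0.50: 0.30 × 0.50 = 15.0%
- q′ = 0.75: 0.30 × (0.156 + 0.516) = 20.2%

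Over response 50–70%, foot pain 20–40%, q of 30% or 50%, and q′ from half to 1.5 times q, the result runs from 4.2% to 28.0%.

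**5. The same effect seen in the clinic proportion.** If people with OA are r times as likely to attend, a true proportion p appears as p·r/(p·r + 1 − p). With p = 0.20 (assumed): r = 1.25 gives 0.25/1.05 = 23.8%; r = 1.5 gives 0.30/1.10 = 27.3%; r = 2 gives 0.40/1.20 = 33.3%; r = 0.5 gives 0.10/0.90 = 11.1%. The sign depends on r, which the documents do not give.

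**6. Sampling error does not cover this.** The 95% half-width at n = 506 is 1.96 × √(0.5 × 0.5/506) = 4.4 points, or 4.0 points at a proportion of 30%. It reflects neither the foot-pain stage nor non-participation.

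**7. Whether another section repairs it.** Multiple imputation appears under Features associated with foot OA phenotypes and under The presentation and diagnosis of OA in primary care, in both cases for missing primary outcome data. Phase 3 compares attenders with non-attenders on health care use only. The Discussion concedes only that people without symptoms are not examined. None of these is carried into the frequency estimate.

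**The case against.** The best defence is that aim (i) and the analysis agree with each other. Both speak of frequency and co-occurrence, as does the Discussion, and descriptive statistics suit that aim. Only the abstract uses the word prevalence, and it does not use the phrase population prevalence. A condensed article may also leave denominators and weights to a fuller document. This narrows the point but does not remove it: the abstract sets the quantity, the article names the method, and that method, followed as written, does not estimate it.

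Three stronger readings are tempting and should not be adopted.

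- A reader might infer that the result describes a self-selected 6% of the population. The 5.6% mixes eligibility with participation. Moreover, 506 is the number required for power, not a forecast, and every consenting responder with foot pain is invited.
- A reader might infer that the claim that the study "will combine unselected population sampling of older adults" is false. It is fairly read as describing the frame: all registered adults in the age range, whether or not they consult.
- A reader might infer that self-selection is disregarded. Reminders, a repeat questionnaire, taxi travel, re-booking letters and reimbursed expenses are all planned. They reduce non-participation, although they do not adjust an estimate for it.

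**Conclusion.** The point holds as a mismatch between the quantity in the abstract and the quantity that the planned analysis yields. The step from x-rays at the clinic to a frequency among symptomatic attenders is an inference, but a safe one, since no other participants are x-rayed.

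The size cannot be fixed from the documents. On the assumed inputs, the denominator alone turns 50% into 10% to 20%, and the wider range with selection is 4.2% to 28.0%. A reader might infer that the clinic frequency overstates OA because people with worse feet are keener to attend. That is plausible, but nothing in the documents establishes the direction or the size.

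The omission of people without symptoms does not prevent estimation of symptomatic prevalence, because they are non-cases by definition. The change is worth making, but it does not touch the stated primary aim, the 3-year comparison of functional outcome by radiographic OA.

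**What to change.** In the section Patterns of symptomatic radiographic foot OA:

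- Define the target population as adults aged 50 and over registered with the four practices, and say how GP exclusions are treated.
- Estimate prevalence in two stages: foot-pain prevalence from the Phase 1 survey, times the proportion with radiographic OA among people with foot pain.
- Account for non-participation by inverse-probability weights. Model survey response on the variables available from the practice list, and clinic attendance on Health Survey variables such as age, gender, BMI from self-reported height and weight, foot pain intensity, the Manchester index and hallux valgus. Multiple imputation of radiographic status in eligible non-attenders is an alternative, not an equivalent: weighting models participation, imputation models the outcome, and the answers can differ.
- Give confidence intervals that reflect both stages, for example by bootstrap.
- Keep the unweighted figures, labelled as among clinic attenders with foot pain.

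If this is not done, restrict the abstract to frequency among clinic attenders with foot pain.

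The cost is extra analysis on survey data already planned for all responders, and somewhat wider intervals. No further data collection from participants is needed. Both methods rest on the measured variables explaining participation well enough, and this should be stated with the result.
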